#### **5.4 Subject Replacement**

There will be no replacement of subjects who have received study medication. Subjects who have permission and assent forms signed but withdraw before receipt of study medication will be replaced.

#### **5.5 Follow -up of Withdrawn Subjects**

If a subject withdraws from the study before the final visit then, if possible, all the Day 28 assessments will be completed. If the subject cannot attend for a final assessment then as a minimum, the End of Study Form must be completed. If a subject withdraws due to an adverse event then the subject must be followed until the event ends or stabilises.

---

## 6 TREATMENT OF SUBJECTS

### 6.1 Study Products

Subjects will receive a single oral dose of vaccine or placebo. The oral route of administration is the normal route of entry for *S. typhi* hence it is appropriate to administer the vaccine by the same route. M01ZH09 is supplied as a freeze-dried formulation of the vaccine strain, plus excipients, in single dose vials. The excipients are shown in Table 4 below;

**Table 4: Excipients included in the single dose vials**

There will be two groups; 100 subjects will be randomised to receive a nominal dose of  $5 \times 10^9$  CFU of M01ZH09 and 50 subjects will be randomised to receive placebo.

Group 1. Active, consisting of  $5 \times 10^9$  CFU of M01ZH09 vaccine strain *S. typhi* (Ty2 aroC ssaV) ZH9 administered in a bicarbonate solution.

Group 2. Placebo, consisting of the vaccine excipients administered in a bicarbonate solution.

The bicarbonate solution is made from an effervescent bicarbonate tablet containing 2.6 g sodium bicarbonate, 1.65 g ascorbic acid and 30 mg aspartame. Each bicarbonate tablet will be dissolved in 150 mL of drinking water. The vaccine or placebo will be dissolved in the appropriate volume of this solution containing 1.75% (w/v) sodium bicarbonate, 1.1% (w/v) ascorbic acid and 0.02% (w/v) aspartame.

Subjects aged 5 to 10 years will receive the vaccine or placebo in 75 mL of bicarbonate solution. Subjects aged 11 to 14 years will receive the vaccine or placebo in 150 mL of bicarbonate solution.

### 6.2 Method of Administration of Each Dose

The method for the reconstitution and administration of the vaccine will be detailed in a separate document provided to the Pharmacist and Investigator.

Subjects will fast for at least 2 hours prior to taking the dose of medication and for 90 minutes after dosing (nothing to eat or drink, with the exception of water). The subject will remain at the Investigative site, under observation, for at least 90 minutes following dosing.

### **6.3 Packaging and Labelling of Study Products**

Vials of IMP and bicarbonate tablets will be provided to the study site in cartons. One carton will contain one vial and one bicarbonate tablet.

Each glass vial will be labelled with the following information as a minimum:

Study Number: MS01.08

Subject Number:

M01ZH09 oral typhoid vaccine or placebo

Caution: New Drug - Limited by Law to investigational use

FOR ORAL ADMINISTRATION ONLY

Keep refrigerated at 2°C to 8°C. DO NOT FREEZE

Packaging reference number:

Emergent Product Development UK Ltd, [name], UK

Each tablet will be labelled with the following information as a minimum:

Study Number: MS01.08

Subject Number:

Bicarbonate tablet for live attenuated vaccine (contains 2.6 g sodium bicarbonate, 1.65 g ascorbic acid and 30 mg aspartame)

Caution: New Drug - Limited by Law to investigational use

For oral use dissolved in water in accordance with the pharmacy instructions.

Not to be swallowed directly.

Store between 2°C and 27°C

Lot number:

Packaging reference number:

Emergent Product Development UK Ltd, [name], UK

The cartons will be sealed with tamper evident seals. The labels will contain as a minimum:

Study Number: MS01.08

Subject Number

M01ZH09 oral typhoid vaccine or placebo, plus bicarbonate tablet

Caution: New Drug - Limited by Law to investigational use

FOR ORAL ADMINISTRATION ONLY

Keep refrigerated at 2°C to 8°C. DO NOT FREEZE

Lot / Packaging reference number:

Sponsor: Emergent Product Development UK Ltd, [name], UK

Investigator: [name], Hospital for Tropical Diseases, Ho Chi Minh City, Viet Nam

### **6.4 Storage and Drug Accountability of Study Products**

Vials of study medication must be kept refrigerated at 2°C to 8°C.

The responsible pharmacist will maintain a Medication Accountability Log. This will include the date, description and quantity of study medication received at the study site, as well as a record of when and to whom it was dispensed.

All unused supplies will be retained at site until Emergent Product Development UK Ltd gives instructions for their return or disposal.

No study products may be dispensed to any person not enrolled in the study or used for purposes other than those described in this protocol.

## **6.5 Other Materials**

Emergent Product Development UK Ltd will provide syringes for use during reconstitution of the vaccine, and dosing containers.

## **6.6 Concomitant Medication**

The use of all medication including ‘over the counter’ and herbal products taken in the 4 weeks prior to screening and during the course of the study, up to Day 28, must be detailed in the case report form (CRF). Subjects are to try to avoid all antibiotic/antibacterial use for 14 days before and after dosing. Should a subject require antibiotics he/she must inform the Investigator and may be withdrawn from the study depending on the timing in relation to the vaccination or have their data excluded from the PP analysis. Subjects must not receive any vaccine other than M01ZH09 during the four weeks, post dose, of the study.

Oral contraception is allowed under the protocol. However, should a female subject using oral contraception develop diarrhoea or require antibiotic therapy she will be requested to use additional barrier methods of contraception in combination with a spermicidal preparation.

If a subject has

- a single positive blood culture, or
- a positive stool culture for *S. typhi* at any time after Day 7

he/she must be treated with antibiotics. The first line antibiotic will be ciprofloxacin 20 mg/kg twice daily, taken orally for 10 days. The second line antibiotic will be azithromycin. The dose of azithromycin is dependent upon the age of the subject. Subjects aged 5 to 7 years should receive 5 mL (200 mg) orally once daily for 7 days, subjects aged 8 to 11 years should receive 7.5 mL (300 mg) orally once daily for 7 days and subjects 11 to 14 years should receive 10 mL (400 mg) orally once daily for 7 days. The third line antibiotic is trimethoprim 40 mg/sulfamethoxazole 200 mg per 5 mL of suspension twice daily, 10 mL taken orally for 10 days. In all cases antibiotic therapy will be initiated as soon as the culture results are known.

Any subject who returns for unscheduled visits after Day 14 and has positive blood or stool cultures for *S. typhi* will be treated as a potential carrier and treated with antibiotics and followed up until the infection is clear. Antibiotics will be administered as outlined above at the discretion of the Investigator. The duration of treatment may be up to 28 days to ensure the infection is clear.

The vaccine strain has been shown to be sensitive to ciprofloxacin, azithromycin and trimethoprim/sulphamethoxazole. Ciprofloxacin has been shown to be the treatment of choice for chronic carriers of wild type *S. typhi*.

Anti-pyretic medications (for example, aspirin, ibuprofen, naproxen sodium) should not be taken for minor aches/pains or injuries as such medication may mask a fever. Paracetamol is an

appropriate concomitant medication for these purposes. Should a subject experience a fever (body temperature = 38.5°C) it is important that he/she contact the investigative site and visit to be assessed. Subjects or their parents/guardians should not initiate anti-pyretic medication unless instructed to do so by the Investigator. Anti-pyretics may be administered under the direction of the Investigator for the management of a diagnosed fever.

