#### **Safety Data (MS01.04)**

The majority of subjects (84%) in the study reported at least one post-vaccination adverse event. A total of 15 (94%) of subjects that received M01ZH09 in presentation 1 reported 44 events. In comparison a total of 12 (75%) subjects that received M01ZH09 in presentation 2, reported 51 events. The majority of the events were gastrointestinal or nervous system disorders.

Gastrointestinal disorders were reported by 8 (50%) subjects in each presentation group. The commonest events specific to the gastrointestinal system were loose stools, which were reported by 4 and 2 subjects for presentations 1 and 2 respectively and abdominal pain, which were reported by 3 and 1 subject(s) respectively. Nervous system disorders were reported by 6 (38%) subjects in presentation 1 and by 10 (63%) subjects in presentation 2. The commonest event specific to the nervous system was headache, which was reported by 6 and 9 subjects for presentations 1 and 2 respectively. Respiratory, thoracic and mediastinal disorders were reported by 3 (19%) subjects receiving presentation 1 and 5 (31%) subjects receiving presentation 2.

There were no deaths or SAEs reported. The majority of events were of mild or moderate severity with only 7 of the 95 events being reported as severe.

There was little difference between the presentations in terms of the occurrence of adverse events.

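### Section 6.6 needs two reconciliations: the azithromycin age bands overlap at 11 years, and the paracetamol permission clashes with the reason given for restricting antipyretics

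*Protocol*

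**What the plan says.** Both points lie in Protocol Section 6.6 (Concomitant Medication).

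**Azithromycin.** Antibiotic treatment is compulsory after one positive blood culture, or after a stool culture positive for *S. typhi* later than Day 7. Ciprofloxacin is first line and azithromycin second. For azithromycin, "The dose of azithromycin is dependent upon the age of the subject". There are three bands. The youngest covers ages 5 to 7, at 200 mg (5 mL) a day. For the other two the text reads "subjects aged 8 to 11 years should receive 7.5 mL (300 mg) orally once daily for 7 days and subjects 11 to 14 years"; the daily amount for the oldest band is 400 mg, in 10 mL. Every course lasts one week.

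**Antipyretics.** Antipyretic drugs, with aspirin, ibuprofen and naproxen sodium as examples, "should not be taken for minor aches/pains or injuries as such medication may mask a fever". The next sentence calls paracetamol an "appropriate concomitant medication for these purposes". After a sentence on what to do about a fever, the section says that children and parents are not to start an antipyretic on their own. The Investigator may direct one for a fever that has been diagnosed.

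**The concern.** The azithromycin bands are inclusive and share an endpoint, so staff treating an 11-year-old could follow either clause and be within the protocol.

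The antipyretic text gives a reason, that a fever might be hidden, and then permits a drug to which the same reason applies. Paracetamol lowers temperature. The protocol does not say so; this is general pharmacology.

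Temperature carries much of the safety design:
- A temperature of 38.5°C or more within 14 days of dosing, attributed to study medication, is a secondary safety endpoint (Section 3.3.2).
- Counts of moderate (38.5°C) and severe (39.5°C) fever suspend dosing (Section 4.8.1, Table 1).
- Fever prompts unscheduled visits. The only automatic triggers for a blood culture are 39.0°C twice in 48 hours or 39.5°C once (Sections 6.8.10 and 7.2.1). The study schedule has no routine blood culture, and one culture positive for *S. typhi* suspends dosing.

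A hidden fever could therefore also mean a culture not taken.

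**Working it through.** **Azithromycin**

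Inputs: the three bands in Section 6.6 and the eligible age range of 5 to 14 years inclusive (Section 5.1).

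1. Internal check of the stated pairs, strength = mg / mL: 200/5 = 40, 300/7.5 = 40, 400/10 = 40 mg/mL. The volumes and milligrams agree in every band, so the fault is in the age limits.
2. Assign each whole year of age to every band that contains it:
   - 5, 6, 7: one band (200 mg)
   - 8, 9, 10: one band (300 mg)
   - 11: two bands (300 mg and 400 mg)
   - 12, 13, 14: one band (400 mg)

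   No eligible age is left without a band.
3. Size at age 11, course total = daily dose × 7: 300 × 7 = 2,100 mg; 400 × 7 = 2,800 mg. Ratio 400/300 = 1.33, a 33% difference.
4. Reach. At least 70% of each group is aged 5 to 10 (Section 4.3), so at most 30% × 100 = 30 vaccinees are aged 11 to 14. Assuming even spread over the four years, 30/4 = 7.5, or 7 to 8 vaccinees aged 11. Only those who need antibiotics and go on to second line would meet the conflict.

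Elsewhere the protocol divides ages without overlap, at 5–10 and 11–14 (bicarbonate volume in Section 6.1, weight limits in Section 5.2). Those places show that the overlap is not a convention of the document, but they do not settle which azithromycin band applies.

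**Antipyretics**

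No arithmetic applies. Side by side, Section 6.6 makes three statements:
- A: antipyretics are restricted for minor aches, because they may hide a fever.
- B: paracetamol is acceptable for those same aches.
- C: families do not start an antipyretic without instruction, and no exception is named.

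A parent who gives paracetamol for an ache follows B. If paracetamol counts as an antipyretic, the same act breaks C as written and runs against the reason given in A.

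On recording, Section 6.6 requires all medication in the CRF, and concomitant medication is reviewed at every visit. Nothing in Section 6.6 or the Diary Card section (7.2.4) asks for a temperature or a clock time before an antipyretic dose. Scheduled home readings are in the morning and at bedtime.

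**The case against.** **On azithromycin.** The overlap may never matter. It concerns second-line treatment after a positive culture, and the adult studies in Section 2.4 report no shedding beyond Day 7 and no blood culture positive for the vaccine strain. This stands as a limit on reach. A reader might infer that every 11-year-old is affected; the text does not support that. Second-line use is still foreseeable: exclusion criterion 4 removes only children hypersensitive to two or more of the three antibiotics, so a child hypersensitive to ciprofloxacin alone may enrol.

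**On paracetamol.** The exemption may be deliberate, and the ban on self-started antipyretics sits between two sentences about fever, so it can be read as applying to fever only. That reading softens the clash between B and C. It does not touch the clash between B and the reason given in A.

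There are also safeguards: clinic temperatures at each visit, daily to Day 14, paired home readings, extra readings if a child feels feverish, and daily medication review. Users can be identified. What is missing is the temperature and time before the dose.

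**A stronger reading to resist.** A reader might infer that vaccinees will take more paracetamol and that the fever difference is therefore biased towards zero. The starting point would be the MS01.04 safety summary: "The commonest event specific to the nervous system was headache, which was reported by 6 and 9 subjects for presentations 1 and 2 respectively", and 9/16 = 56% with the presentation used here. Section 2.7 also expects headache and mild muscle and joint pain with the active vaccine. But MS01.04 was open, in adults and without placebo, and a headache is not a paracetamol dose. MS01.07 was placebo-controlled, used the same solution in Vietnamese adults, and reported no apparent difference from placebo in headache and no adverse event that needed medication. MS01.03 found no significant vaccine–placebo difference in adverse events. Greater use in vaccinees is possible but not shown. A count of missed fevers would need a fever rate, an uptake rate and a masking rate, none of which the protocol gives.

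**Conclusion.** Both inconsistencies are real and should be corrected.

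The azithromycin rule gives two doses for age 11, differing by one third (2.1 g against 2.8 g over 7 days), and nothing else in the protocol resolves it. The consequence is confined to 11-year-olds who reach second-line treatment, probably very few, and no endpoint depends on it.

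The antipyretic sentences conflict with their own stated reason and, on a plain reading, with each other. This rests on one assumption outside the text, that paracetamol is an antipyretic. It matters because recorded temperature drives a safety endpoint and several safety actions. Within an arm, masking could only lower the recorded fevers. How far, and with what effect on the comparison between arms, cannot be computed from the documents.

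**What to change.** - The sponsor must reconcile the azithromycin bands so that each age falls in one only. This review takes no view on which dose applies.
- The sponsor must reconcile the three antipyretic statements so that families and staff have one rule for paracetamol. This review takes no view on what that rule should be.
- Whatever is decided, add a Diary Card field for oral temperature and clock time before any dose of paracetamol or another antipyretic.
- Summarise antipyretic use in Days 0 to 14 by arm, beside the fever results. Keep users in the fever analysis. Antipyretics are allowed under the Investigator's direction for a diagnosed fever, so leaving users out would remove treated fevers, which may be the endpoint events themselves. The summary is descriptive, since use arises after randomisation.

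Cost: protocol wording, one Diary Card field, one table and a small extra task for parents.

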## **6.7 Compliance**

The study staff will administer the study medication and observe the subjects' compliance.

## **6.8 Visits and Procedures**

### **6.8.1 Screening period (Day –28 to Day –1)**

The parents or guardians of all subjects will provide written permission before any study related procedure is carried out. Where appropriate, with regard to age and understanding, the subject will be asked to sign an assent form indicating their willingness to take part in the study. After written permission has been obtained, the subject will be allocated a 'Screening Number' which will be used, together with his/her initials as their unique identifier until dosing at Visit 1. The following will be recorded/performed:

- Demographic data
- Medical history, including any allergies, and vaccination history
- Prior concomitant medications (in previous 4 weeks before screening), particularly antibiotic use and including herbal and over the counter medications
- Physical examination including height, weight and vital signs (blood pressure, temperature and pulse) and an examination for any signs of splenomegaly.
- Draw blood for:
  - Serum biochemistry and haematology (Section 7.2.1)
  - HIV test
- Obtain urine sample for:
  - Urine pregnancy test (females of 11 years and older only)
  - Dipstick test, and if the dipstick is positive for leucocyte esterase and nitrites, a separate sample will be sent for microscopy, culture and sensitivity
- Obtain stool sample for culture for *Salmonella spp.*
- Make an appointment for suitable subjects to attend for Visit 1 (randomisation and administration of the study medication) within the next 4 weeks. Instruct subject to bring a stool sample to the next visit.

### 6.8.2 Visit 1: Day of Dosing/ Day 0

This visit should take place within 28 days of the screening visit, following receipt of the full laboratory results. After the laboratory results have been reviewed, those subjects who continue to meet the inclusion criteria, and do not meet any of the criteria for exclusion, will continue in the study. The following tasks will be performed:

- Collect stool sample subject has brought to clinic. (Note: This sample will not be cultured prior to dosing but if it is subsequently shown to be positive for any Salmonella strain the data from the subject will be excluded from the PP analysis).
- Review the inclusion and exclusion criteria for continued study eligibility
- Review medical history and record any changes since screening
- Enquire about and record any adverse events since the last visit (see Section 6.8.9) to include an examination for any signs of splenomegaly
- Enquire about and record any changes in concomitant medication since screening

**If the subject has received antibiotic therapy within 14 days of this visit, arrange for the subject to return for dosing if this is possible within 28 days of the screening visit. If not, please withdraw the subject from the study.**

**Subjects who are withdrawn at Visit 1, under these circumstances and cannot be dosed within 28 days of the Screening Visit may be re-screened. Under these circumstances the subject must be re-consented.**

If the subject remains eligible:

- Determine and record vital signs (blood pressure, temperature and pulse)

**If oral temperature is 38°C or more, arrange for the subject to return for dosing if this is possible within 28 days of the screening visit. If not, please withdraw the subject from the study.**

**Subjects who are withdrawn at Visit 1, under these circumstances and cannot be dosed within 28 days of the Screening Visit may be re-screened. Under these circumstances the subject must be re-consented.**

- Obtain urine sample for:
  - Urine pregnancy test (females aged 11 years and older only)
  - Dipstick test, and if the dipstick is positive for leucocyte esterase and nitrites, a separate sample will be sent for microscopy, culture and sensitivity
- If the subject remains eligible, allocate the next available age-group specific Subject Number to the subject and enter this into the Visit 1 header of the CRF and the associated medication pack bearing this 'Subject Number'.
- Draw blood for:
  - Serum biochemistry and haematology
  - Serum IgG (ELISA assay)

- Serum IgA (ELISA assay)
  - Determining the number of ASC secreting IgA (ELISPOT assay; only for subjects aged at least 11 years and weighing at least 27 kg)
- After ensuring that the subject has fasted for at least 2 hours, administer the dose of study medication (if the subject vomits within 1 hour of administration then he/she will need to receive a repeat dose).
- Record pulse and blood pressure at 30, 60 and 90 minutes after dosing
- Subjects will remain at the study site for at least 90 minutes following administration of study medication so that any adverse events may be recorded.
- Subjects must not eat or drink (with the exception of water) for 90 minutes following vaccination
- Issue a digital thermometer for recording body temperature orally. Subjects and their parents/guardians will be instructed to take body temperature readings each day in the morning when they get up and in the evening when they go to bed and to record the measurement in the Diary Card.
- Issue a Diary Card and instruct the subject and their parents/guardians on its completion (Section 7.2.4)
- Make an appointment for Visit 2/ Day 1 and instruct the subject to bring a stool sample to the visit.

### 6.8.3 Visit 2: Day 1

The subject will return to the clinic approximately 24 hours after dosing, where the following assessments will be completed:

- Collect the stool sample that the subject has brought to the clinic for culture of vaccine strain *S. typhi* (Ty2 *aroC* *ssaV*) ZH9
- Determine and record vital signs (blood pressure, temperature and pulse)
- Review Diary Cards and summarise data in CRF
- Enquire about and record any adverse events since the last visit (see Section 6.8.9) to include an examination for any signs of splenomegaly
- Enquire about and record any changes in concomitant medication since the last visit
- Make an appointment for Study Day 2 and instruct the subject to bring a stool sample to the visit

### 6.8.4 Visits 3, 4, 5, 6 and 7: Days 2, 3, 4, 5 and 6

The subject will return to the clinic where the following assessments will be completed:

- Collect the stool sample that the subject has brought to clinic for culture of vaccine strain *S. typhi* (Ty2 *aroC* *ssaV*) ZH9

- Determine and record vital signs (blood pressure, temperature and pulse)
- Review Diary Cards and summarise data in CRF
- Enquire about and record any adverse events since the last visit (see Section 6.8.9) to include an examination for any signs of splenomegaly
- Enquire about and record any changes in concomitant medication since the last visit
- Make an appointment for a clinic visit on the following day and instruct the subject to bring a stool sample to the visit

